## **1. Background and rationale**

The Oxford Mental Illness and Suicide (OxMIS) risk assessment tool was first published in 2019. This prediction model was originally developed in Sweden using population-based registers, and estimates the risk of suicide in patients diagnosed with a severe mental illness (e.g., schizophrenia-spectrum disorders or bipolar disorder). The model was developed using a standard statistical approach (multivariable logistic regression models) and includes 17 pre-specified risk markers based on clinical, socio-demographic, and criminal history variables.

The OxMIS tool generates a probability score of suicide risk within 12 months following discharge from medical care for a psychotic episode, based on 17 predictors. Certain of these risk markers can be imputed as 'unknown' if missing, in which case, the model returns a range of predictive probabilities. OxMIS is intended to support clinical decision-making. It is a significant improvement compared with current suicide risk tools due to the high methodological quality of its development and validation, scalability and ease of use, transparency, and publication of a full range of performance measures (including its discrimination and calibration). Research protocols underlying model development and final coefficients have been published. The model is currently being externally validated in the UK using electronic health record data, and a recent study found it was a feasible approach.

## **2. Objectives and outcome measures**

The objective of the current study is to assess the predictive performance of OxMIS using data from a cohort of patients diagnosed with a severe mental illness in Finland between 1996 and 2017.

The outcome measure, completed suicide within 12 months, will be extracted from the Finnish Causes of Death Register, which includes the main and contributory causes of all deaths recorded in the whole country throughout the time period according to the tenth revision of the International Classification of Diseases (ICD-10). Consistent with the original study and research literature, we will include both certain (ICD-10: X60-X84) and uncertain (ICD-10: Y10-Y34) deaths by suicides.

### **3. Study design**

We will conduct a case-control study of discharged patients with severe mental illnesses and an external validation of the existing OxMIS tool. No new data will be collected as we will use existing routinely collected data from the Finnish nationwide registries.

### **4. Participant identification and recruitment**

#### **4.1. Study participants**

Participants will be individuals who were diagnosed with a severe mental illness in Finnish hospitals.

#### **4.2 Inclusion criteria**

Residents of Finland who were diagnosed with a severe mental illness between 1 January 1996 and 31 December 2017.

#### **4.3 Exclusion criteria**

Individuals who were younger than 15 years or older than 65 years at the time of the discharge.

### **5. Statistics and analysis**

#### **5.1 Description of statistical methods**

##### *Performance measures*

We will evaluate the calibration and discrimination of the model as recommended in current expert guidelines. Calibration refers to the agreement between the predicted and observed outcomes, while discrimination refers to the ability to distinguish individuals who have died from suicide and those who have not based on a predetermined cut-off (which was set at 1% in the original study).

Calibration is usually evaluated graphically through calibration plots, which compare the relationship between observed and predicted outcomes to a diagonal line. Discrimination tests how well a model differentiates different risk categories, and examines true and false positives and negatives. The most

common overall measure of discrimination is the area under the curve (AUC) for specific follow-up times and c index for varying follow-up periods.

### *Strategy for analysis*

We will employ an incremental strategy to assess the prognostic performance of OxMIS in the Finnish cohort. First, the individual-level prognostic performance will be evaluated in a simple validation perspective, without any adjustment of the model coefficients for the Finnish population. If the model performs poorly in this new population, it will be updated according to a series of pre-specified steps detailed below.

The following steps will be undertaken, proceeding in each case to the subsequent stage only if diagnostic performance is insufficient. The assessment of prognostic performance between steps (i) to (iv) below will be based on statistical significance (retaining the simplest version model for which the subsequent step provides no statistically significant improvement) and the final assessment of performance based on clinical utility – with a particular focus on the equivalent measures reported in the model development paper.

- i. Simple validation: assess the prognostic performance of the existing OxMIS model directly using the Finnish data by applying the existing model directly, without adjusting model coefficients and without adjusting the estimate of baseline risk.
- ii. Updating the baseline risk (analogous to the intercept), holding coefficients of predictor variables at their values from the current model. This may also be seen as adjusting for any systematic risk difference that may be attributable to missing covariates (see subsection below).
- iii. Updating the baseline risk and performing a simple re-calibration of the coefficients of the predictors. This allows for the inclusion of a single re-calibration parameter, i.e. the effect of predictors on the outcome would be assumed to be the same as in the original study, apart from rescaling.
- iv. Additionally re-estimating a subset of the model coefficients. This will be performed only as a last resort as it is likely to lead to a substantively different prediction tool and would allow the associations of the risk markers with the outcome to differ from those found in the original study. If possible, re-estimation will be restricted to a subset of parameters whose coefficients appear to be poorly calibrated.

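### The rule for choosing an updating step can stop at the intercept test and keep the unmodified model without ever testing its calibration slope

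*Protocol*

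**What the plan says.** Protocol, section 5.1, Strategy for analysis, first applies the model unchanged. A conditional sequence follows: "If the model performs poorly in this new population, it will be updated according to a series of pre-specified steps detailed below", with the analysts "proceeding in each case to the subsequent stage only if diagnostic performance is insufficient".

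The next sentence makes statistical significance the criterion for judging one step against another, with the analysts "retaining the simplest version model for which the subsequent step provides no statistically significant improvement". Clinical utility enters only afterwards, as the basis for "the final assessment of performance based on clinical utility".

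The steps are nested. Step (ii) is "Updating the baseline risk (analogous to the intercept), holding coefficients of predictor variables at their values from the current model". Step (iii) adds the slope: "This allows for the inclusion of a single re-calibration parameter". Step (iv) re-estimates some coefficients, with the caution "This will be performed only as a last resort as it is likely to lead to a substantively different prediction tool".

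Section 5.2 expects more than 137,000 individuals and, at a one-year suicide risk of 0.8%, 1,096 suicides.

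**The concern.** A prediction model can be miscalibrated in two separate ways: its average risk can be off (intercept), or its predictions can be too spread out or too compressed (slope). The sequence tests these one after the other, and the first test decides whether the second takes place. A model with the right average and the wrong slope gives a non-significant comparison of (i) with (ii). The rule then calls for the simplest model to be kept, and (ii) is never compared with (iii).

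What is at stake is which model is retained. Under Predicted probabilities, the Protocol presents results mainly as risk probabilities, and under Performance measures it refers to a 1% cut-off, so an error in the spread of individual risks matters. Matching average risk is also a plausible case: section 5.2 plans on the same 0.8% as the original cohort, and the Predictors subsection stresses how similar the two countries are.

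**Working it through.** **Inputs from the Protocol.** N = 137,000 and one-year risk 0.8% (section 5.2); the retention rule and the content of steps (i) to (iii) (section 5.1).

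**Assumptions not in the Protocol.** Two-sided 5% level; likelihood-ratio tests; a normally distributed linear predictor with SD 0.6, 0.9 or 1.2.

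**1. The plan's own figure.** 137,000 × 0.008 = 1,096 events, and 1,096 / 100 = 10.96, which is the stated factor of nearly 11. It reproduces exactly.

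**2. What the (i) versus (ii) test can see.** With the linear predictor as a fixed offset, the intercept test depends on observed minus expected events. The slope does not enter.
- SE of the intercept shift ≈ 1 / √(1,096 × 0.992) = 0.0303.
- Non-significant range for O/E: exp(±1.96 × 0.0303) = 0.942 to 1.061, or about 1,033 to 1,163 suicides observed against 1,096 expected.
- If true O/E is 1.0, the test is non-significant with probability of about 95%, whatever the slope.

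**3. How wide the window is.** By the same formula, the chance that the intercept test is significant is about 37% at true O/E 1.05, 49% at 1.06, 89% at 1.10 and 99.6% at 1.15. Once it is significant, the slope is reached. The problem therefore belongs to cohorts whose average risk nearly agrees with prediction.

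**4. Simulation of the sequence.** 200 runs per row, with true O/E 1.0 and mean predicted risk 0.8%:

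| SD of linear predictor | True slope | Sequence stops at (i) | Joint 2-df test of (i) vs (iii) significant |
|---|---|---|---|
| 0.6 | 0.7 | 94.5% | 100% |
| 0.9 | 0.7 | 93.5% | 100% |
| 1.2 | 0.7 | 95.5% | 100% |
| 0.6 | 0.5 | 94% | 100% |
| 0.9 | 0.5 | 96% | 100% |
| 1.2 | 0.5 | 95% | 100% |
| 0.6 | 0.9 | 94.5% | 41% |
| 0.9 | 0.9 | 93% | 75.5% |
| 1.2 | 0.9 | 97% | 92.5% |
| 0.6 | 1.0 | 96.5% | 3.5% |
| 0.9 | 1.0 | 93.5% | 6% |
| 1.2 | 1.0 | 95.5% | 4.5% |

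The stopping rate hardly depends on the slope. Separate simulations of O/E 1.0 with slope 0.7 stopped at (i) in 38 of 40 runs (17 assumed binary predictors), in 95 of 100 at each SD, and in 83% to 97% in a further set. The last three rows show that the joint test does not raise the false-update rate when the model is correct.

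**5. What the retained model would look like.** At SD 0.9 and slope 0.7, it predicts 4.21% at the 99th percentile where the true risk is 2.79%, and 0.17% at the 10th percentile where the true risk is 0.29%.

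**The case against.** The best reply is that significance is not the only gate. Updating starts only if the model performs poorly and continues only if performance is insufficient. An analyst who saw a slope of 0.7 could call that insufficient and go on. The numerical meaning of those words, the test and the level may also be set in an analysis plan that is not at hand. In addition, step (i) is carried out in every case, and Presentation of results commits to calibration plots, so a poor slope would be visible to readers.

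Part of this stands. The unmodified model's calibration will be shown, so the harm is limited to which model is retained, and only when O/E is close to 1. But the gates do not remove the problem. The condition is worded as necessary for moving on, and the retention rule still says to keep (i) when (ii) adds nothing significant. Nothing links the plots to the choice of step, and clinical utility comes after that choice.

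Three stronger readings are tempting but not supported:
- A reader might infer that, with this many events, the rule will update models whose miscalibration is trivial. The insufficiency condition can block that. The chance of a significant intercept test at O/E 1.05 is only 37%, and an intercept update at O/E 1.10 (0.80% to 0.88%) leaves every coefficient in place and improves calibration.
- A reader might infer that a p-value alone can trigger step (iv). The text makes it a last resort and, where possible, confines it to coefficients that look poorly calibrated.
- A reader might object that steps (ii) and (iii) cannot raise the AUC. The Protocol never says they do, so this is not an error in it.

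**Conclusion.** The point holds in limited form and should be fixed before the analysis. Read literally, the rule lets a non-significant intercept test end the sequence. When average risk agrees with prediction, it keeps the unmodified model in roughly 95% of runs at a true slope of 0.7, a misfit that a joint test finds in essentially all of them. The consequence is confined to O/E of about 0.94 to 1.06 with 1,096 events.

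The size rests on the assumed 5% level, likelihood-ratio tests and a normal linear predictor. The mechanism needs only that steps are compared one at a time and that step (ii) moves only the intercept. The documents do not support saying that the unmodified model would be declared valid for Finland, since retention is not the same as the final assessment.

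**What to change.** Reword the selection rule in section 5.1, Strategy for analysis, so that:
- O/E (or the intercept) and the calibration slope are estimated with 95% confidence intervals for the unmodified model at step (i);
- (i) is compared with (iii) jointly on 2 degrees of freedom, and the choice between (ii) and (iii) is made only after that, so that a non-significant intercept test alone cannot end the sequence;
- statistical significance does not replace the insufficient-performance condition, and the sizes of O/E and slope are read alongside the p-value, because about 1,096 events make small deviations likely to be significant.

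The team may set numerical tolerances in advance. For example, it could use O/E 0.80 to 1.25 and slope 0.9 to 1.1, but these are illustrations, and statisticians may reasonably choose others.

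The cost is a reworded paragraph and one extra comparison between models already to be fitted. No new data are needed.

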### *Presentation of results*

Findings will be presented using both calibration and discrimination, graphically and using tables and summary statistics as appropriate. These will include calibration plots; sensitivity and specificity; AUC.

The report will include descriptive information about the cohort and how it was defined, including any differences from the original cohort in definitions of variables. As far as possible we will follow published guidance on reporting validation study results.

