## 5.2 The number of participants

Preliminary data suggest a total sample size exceeding 137,000 individuals, nearly twice that of the original study (n=75,158). A simulation study recommended ballpark minimum figures of 100 events for validating a clinical prediction rule derived using a logistic regression model. If we were to identify an equivalent baseline one-year suicide risk rate as in the original study (0.8%), we would thus have nearly 11 times as many outcome events (i.e. suicides) as the minimum recommendation for validation studies (1096 vs. 100).

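### The final assessment looks to the Swedish AUC, sensitivity and specificity with no case-mix reference, so a Finnish-Swedish difference in these measures cannot be read as model error or its absence

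*Protocol*

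**What the plan says.** Protocol section 5.1, Strategy for analysis, separates two decisions.

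- **Moving between update steps (i) to (iv).** The team advances "proceeding in each case to the subsequent stage only if diagnostic performance is insufficient" and decides by statistical significance, "retaining the simplest version model for which the subsequent step provides no statistically significant improvement".
- **Final assessment of performance.** This rests on clinical utility, "with a particular focus on the equivalent measures reported in the model development paper". No threshold is set and no other reference is named for discrimination or classification.

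On the measures themselves, Presentation of results states: "These will include calibration plots; sensitivity and specificity; AUC". Performance measures ties classification to a threshold, "based on a predetermined cut-off (which was set at 1% in the original study"). It also says that calibration is judged against the diagonal of the plot. Section 1 notes that the original publication reported both discrimination and calibration.

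On cohort differences, Presentation of results promises a description of the cohort and of differences in variable definitions. It does not say how their effect on the performance figures will be separated from model error.

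**The concern.** The AUC reflects how widely predicted risks are spread in the sample as well as whether the coefficients are right. Sensitivity and specificity at a fixed 1% cut-off also depend on the level of risk. Two cohorts in which OxMIS is equally correct can therefore give different values. Conversely, a more varied cohort can offset weakened coefficients and reproduce the Swedish values.

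The protocol gives reasons to expect some difference. The Finnish cohort runs from 1996 to 2017, while the Swedish study began in 2001 (section 2; section 5.1, Missing data). The violent-crime measure now available is narrower, and two medication predictors were partly imputed in Sweden but are fully recorded in Finland (section 5.1, Predictors and Missing data).

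At stake is the reading of the headline discrimination and classification results. A lower Finnish AUC could be reported as OxMIS failing in Finland when the cohort is merely more homogeneous. An equal AUC could be taken as confirmation when it is not.

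**Working it through.** **Inputs from the protocol (5.1, 5.2).** Finnish sample 137,000; Swedish sample 75,158; one-year risk 0.8%; cut-off 1%.

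**Assumptions.** The document gives neither the development AUC nor the spread of the linear predictor in either country. I take a normal linear predictor with SD 0.7 to 0.9 and, separately, mean risk 0.5% to 1.2%.

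**Step 1. The plan's own figure.** 137,000 × 0.008 = 1,096 events, and 1,096/100 = 10.96. This agrees with section 5.2. The same risk in Sweden gives 75,158 × 0.008 ≈ 601 events.

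**Step 2. Correct model, only case mix changed.** For each SD the mean of the linear predictor is solved to give the stated mean risk. The measures then follow by numerical integration over the predicted risks p:

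- expected sensitivity = sum of p over those with p ≥ 1%, divided by the sum of all p
- expected specificity = sum of (1 − p) over those with p < 1%, divided by the sum of all (1 − p)
- expected AUC = probability that a case outranks a non-case, weighting people by p and by 1 − p

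| SD | Mean risk | AUC | Sensitivity | Specificity |
|---|---|---|---|---|
| 0.7 | 0.8% | 0.689 | 51% | 75% |
| 0.8 | 0.8% | 0.714 | 55% | 75% |
| 0.9 | 0.8% | 0.737 | 58% | 76% |
| 0.8 | 0.5% | 0.714 | 32% | 90% |
| 0.8 | 1.2% | 0.713 | 74% | 57% |

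Hand check for a rare outcome: AUC ≈ Φ(SD/√2). At SD 0.8 this is Φ(0.566) = 0.714.

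**Step 3. Are the AUC shifts large against chance?** The Hanley-McNeil standard error at AUC 0.714 is 0.0088 with 1,096 Finnish events and 0.0119 with 601 Swedish events. For a difference, √(0.0088² + 0.0119²) = 0.0148, a 95% half-width of 0.029. The shifts from SD 0.8 are 0.025 (down) and 0.023 (up). These are 0.025/0.0148 = 1.7 and 0.023/0.0148 = 1.6 standard errors, inside the half-width.

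**Step 4. The same for sensitivity when mean risk changes.** At 0.5% Finland would have 137,000 × 0.005 = 685 events. The standard error of the difference is √(0.32 × 0.68/685 + 0.55 × 0.45/601) = 0.027. The shift is 0.55 − 0.32 = 0.23, more than eight standard errors. The fixed cut-off is therefore more sensitive to case mix than the AUC is.

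**Step 5. Can model error be hidden?** Take SD 1.0 with a true calibration slope of 0.8 and mean risk 0.8%. The AUC is 0.714, sensitivity 53% and specificity 76%, close to a valid model at SD 0.8. If OxMIS were correct at SD 1.0, the expected AUC would be about Φ(1.0/√2) = 0.76. The observed 0.714 lies about 0.046/0.0088 ≈ 5 standard errors below that, so a case-mix reference would show the error.

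**Step 6. What calibration shows.** With a correct model, observed/expected and the calibration slope are 1 under every case mix. The calibration slope has a standard error of about 0.03 to 0.04 at this sample size, so a slope of 0.8 is at least 0.2/0.04 = 5 standard errors from 1.

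An intercept wrong by a factor of 2 behaves differently. With an assumed development AUC of 0.70, the AUC stays at 0.70 and sensitivity at 0.52 to 0.53 while observed/expected becomes about 0.50 or 1.97. Only calibration reveals that error, so expected values alone would not be enough.

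**The case against.** The strongest reply is that the protocol does not make the Swedish values a pass mark. The criterion is clinical utility, no threshold is set, and the phrase about equivalent measures can mean reporting the same metrics. A reader might infer that Finnish values must match Swedish ones; the text does not say so. What remains is that no other reference is named for reading these three measures.

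A reader might also infer that case mix could push the team to the wrong updated model. The documents do not support this. Steps (i) to (iv) are decided by statistical significance, so a correct model would be retained at step (i) apart from chance. Weakened coefficients are what step (iii) tests. Steps (ii) and (iii) cannot change the AUC, because an intercept shift or a positive rescaling preserves ranking. The trigger for updating is undefined, but that is a separate matter.

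Calibration is planned, has an absolute reference and is not distorted by case mix when the model is correct. A failing model is hidden only if discrimination or classification drives the judgement. This reply stands.

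It is also true that the objective in section 2 is performance in Finland. For clinical utility, a lower AUC in a homogeneous cohort is a real property of the tool there. The observed Finnish values should therefore stay the measure of utility, with the expected values used only to explain differences from Sweden.

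Finally, such a benchmark could sit in an analysis plan that is not shown. The protocol itself, however, fixes where the final assessment looks.

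**Conclusion.** The point holds as one of interpretation. The AUC, sensitivity and specificity at 1% depend on case mix, and the final assessment points to their Swedish counterparts without a case-mix reference. Under the assumptions above, an SD change of 0.1 moves the AUC by 0.023 to 0.025, and a mean risk of 0.5% to 1.2% moves sensitivity from 32% to 74% with the model exactly right.

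A reader might compare the AUC shifts with the Finnish half-width alone (1.96 × 0.0088 = 0.017) and call them beyond chance. With the Swedish error included they are not. Larger SD differences would be, but the document gives no basis for choosing one.

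Neither the model-selection rule nor the calibration results are undermined. This is a worthwhile, inexpensive improvement rather than a flaw that invalidates the plan.

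**What to change.** In section 5.1, Strategy for analysis, add three commitments.

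1. The step (i) AUC, sensitivity and specificity at 1% will be reported beside the values expected if OxMIS were correct, computed from the unmodified OxMIS probabilities in the Finnish cohort by the formulas in step 2 above or by simulating outcomes.
2. The mean and SD of the linear predictor and the calibration intercept and slope will be reported with them.
3. Differences from the Swedish values will be attributed to model failure only where observed values depart from the expected ones or calibration is poor. The observed Finnish values remain the measure of clinical utility.

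This benchmark uses the predictors as recorded in Finland. It does not isolate measurement differences such as the violent-crime definition or medication capture, which still need to be described.

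The cost is a short addition to the protocol, a few lines of code on probabilities already needed for step (i), and one extra column in the results table.

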### *Predictors*

The current study will examine all 17 predictors included in the OxMIS tool. A list of the variables that will be employed in this analysis is presented below (see appendix A). Given the geographical proximity and similar healthcare service provision, including the ways in which health care and administrative data are organized, between Sweden and Finland, we expect the predictor definitions to be broadly similar across both countries. One potential difference is the definition of previous violent crime convictions. The original study used a somewhat broader measure of violent crime offences than what is currently available in the Finnish database that we have access to. More detailed conviction data has been applied for and is expected to be delivered before 31 December 2022. The updated data will include specific penal codes, which could be used to derive an analogous measure of violent crime as in the original study. The narrower measure of violent crime that is currently available in Finland has nevertheless been used in a wide range of criminological studies to date.

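### Step (iv) tests coefficients picked because they look wrong in the same Finnish data: once it is considered, unadjusted 5% testing would replace a correct rescaled model about 58–60% of the time

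*Protocol*

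**What the plan says.** Section 5.1 (Strategy for analysis) sets out four steps: (i) apply OxMIS unchanged, (ii) update the baseline risk, (iii) also rescale all predictor effects by one common factor, (iv) also re-estimate some coefficients. Four statements bear on the move from (iii) to (iv).

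- The subset for step (iv): "If possible, re-estimation will be restricted to a subset of parameters whose coefficients appear to be poorly calibrated".
- The comparison between steps "will be based on statistical significance". The model to keep is found by this rule: "retaining the simplest version model for which the subsequent step provides no statistically significant improvement".
- The sequence is gated, "proceeding in each case to the subsequent stage only if diagnostic performance is insufficient". Of step (iv) the protocol adds: "This will be performed only as a last resort". The reason given, with the original study as the comparator, reads: "likely to lead to a substantively different prediction tool and would allow the associations of the risk markers with the outcome to differ".
- At the end comes "the final assessment of performance based on clinical utility".

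The protocol gives no list of eligible coefficients, selection threshold, significance level, degrees of freedom, hold-out sample or multiplicity adjustment. On definitions, the Predictors subsection says: "One potential difference is the definition of previous violent crime convictions".

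**The concern.** The only outcome data in the study are those of the Finnish cohort, so a coefficient can look poorly calibrated only in those data. The same data then supply the significance test. An ordinary test of the freed coefficients takes its reference distribution as if the subset had been named beforehand. Its null hypothesis is that these particular coefficients are right. The null that matters is that no OxMIS coefficient departs from its rescaled original value. When the most deviant coefficients are the ones tested, much of the apparent improvement comes from having selected them.

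At stake is the contrast between steps (iii) and (iv). A false rejection would be reported as evidence that risk markers relate to suicide differently in Finland than in Sweden. A tool with partly noise-driven coefficients would replace one that needed only rescaling.

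**Working it through.** **Inputs from the protocol.** 137,000 people and a one-year risk of 0.8% (section 5.2); 17 predictors (section 5.1, Predictors). Appendix A lists education with three levels, hence two coefficients, so 17 predictors give 18 coefficients.

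**Inputs assumed.** Significance level 0.05, with 0.01 and 0.10 as the range; all coefficients screened without adjustment; in the simulations, predictor prevalences, effects and correlations.

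**The plan's own figure.** 137,000 × 0.008 = 1,096 expected suicides, as section 5.2 states. It states no error rate for the updating steps.

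**False replacement by formula.** If step (iii) is correct and k coefficients are each tested at level α, the chance that at least one looks significant is, with independent tests, 1 − (1 − α)^k.

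| α | k | Result |
|---|---|---|
| 0.05 | 17 | 1 − 0.95^17 = 0.582 |
| 0.05 | 18 | 1 − 0.95^18 = 0.603 |
| 0.01 | 18 | 1 − 0.99^18 = 0.165 |
| 0.10 | 18 | 1 − 0.90^18 = 0.850 |
| 0.05 | 5 | 1 − 0.95^5 = 0.226 |
| 0.05 | 10 | 1 − 0.95^10 = 0.401 |

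**Does dependence between the tests matter?** A score-test simulation used the plan's size, 18 coefficients, a true slope of 0.8, and intercept and slope refitted as in step (iii). Latent correlation between predictors ran from 0 to 0.5.

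- Any of 18 single-coefficient tests significant at 5%: 0.574 to 0.591 (at 1%: 0.159 to 0.164).
- 17 predictors, education tested on 2 df: 0.557 to 0.573.
- Worst-looking 1, 2, 3 or 5 coefficients, tested together on the naive number of df: 0.51 to 0.66.
- Five coefficients named in advance, joint 5-df test: 0.049 to 0.052.
- Joint test of all coefficients against step (iii), 17 df (18 less the one used by the slope): 0.051 to 0.054.

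**Full logistic simulation.** True intercept shift −0.25 and slope 0.8; 400 datasets with independent predictors and 600 with latent correlation 0.3 (latter in brackets). Likelihood-ratio test of (iv) against (iii):

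- worst coefficient, 1 df: 61.8% (60.2%);
- all coefficients with |z| > 1.96: 60.5% (59.3%);
- joint 17-df test: 4.3% (5.7%);
- smallest p below 0.05/18, which is Holm's first step: 5.8% (5.7%).

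Simulation error on a 60% rate from 400 datasets is √(0.6 × 0.4/400) = 0.024, so these agree with the formula. Selection drives the excess: the two rules that allow for it stay close to 5% in the same runs.

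**How often is step (iv) reached?** When each move was decided by significance, the chain reached step (iv) in 97–100% of datasets with the assumed shift and slope. With OxMIS transporting perfectly it did so in 0.5% of 200 datasets. In that case overall false replacement cannot exceed 0.5%, although the worst-coefficient test itself rejected in 65.5%.

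**The case against.** The strongest reply is that step (iv) is fenced in. It is a last resort, entered only when performance is insufficient. If the rescaled model is true, its calibration at step (iii) is right by construction, so on a plain reading step (iv) might never be opened. A reader might infer that a correctly rescaled OxMIS would be replaced about 60% of the time overall. The documents do not support that. The figure is conditional on step (iv) being considered, and the high rate of reaching it above comes from an intercept shift and slope that the protocol does not give.

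The fence is not secure, however. Insufficient performance has no threshold, and the retention rule can be read as keeping step (iii) only if step (iv) fails its test. If the judgement turned on discrimination, steps (ii) and (iii) could not help, because shifting and positively rescaling the linear predictor leaves the AUC unchanged.

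A second reply is that the level, the form of the test and multiplicity are commonly left to a statistical analysis plan, which is not at hand. That stands: the missing level is not a fault, and no error rate can be called a multiple of a stated one. A joint test is not excluded by the text either. But the protocol itself states both how coefficients are selected and how the step is judged, and followed as written the two combine badly.

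Third, a reader might infer that the study could not then say whether OxMIS transports. That goes too far. Step (i) is carried out first and is untouched, and the final assessment rests on clinical utility. No effect on AUC, calibration or classification at the 1% cut-off has been shown.

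**Conclusion.** The point holds in conditional form. Step (iv) selects and tests on the same data without allowance for the selection. Once it is considered, with unadjusted 5% tests of all 17 to 18 coefficients, a correct rescaled model would be replaced about 58–60% of the time. The range is about 16% to 85% over levels of 0.01 to 0.10 for 18 coefficients, and about 23% to 40% at 0.05 with 5 to 10 candidates. Correlation between predictors changes this little. The unconditional rate cannot be derived from the protocol and is very low if OxMIS needs no change at all. The damage is confined to the claim that associations differ from the original study and to which updated tool is kept.

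**What to change.** Replace the last sentence of step (iv) with wording such as:

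> *Step (iv) is entered only if a joint test of all OxMIS coefficients against the step (iii) model is significant at the 5% level, or at least one coefficient departs from its rescaled value after Holm adjustment across all coefficients (one of these to be fixed before Finnish outcomes are examined). With the Holm rule, only the coefficients that pass are re-estimated.*

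If the joint test is chosen, also state which coefficients are then freed, since that test shows that some effect differs but not which one.

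Naming the subset before outcomes are examined is an acceptable alternative. It should not rest on violent crime alone: the Predictors subsection expects more detailed conviction data that may remove that difference, and such a list would bar updating any other predictor that truly differs.

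The change costs one sentence and a p-value adjustment, with no new data. The price is some power to detect a single truly different coefficient. For a departure of 0.4 log-odds, under assumed prevalences, Holm had 70% (self-harm) to 81% (violent crime) power. The unadjusted rule had about 98%, but it also rejects about 60% of the time when nothing differs.
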